### Informed consent

Obtaining informed consent for this trial will be on five levels, as follows.Head teachers: Subsequent to expressing their interest in the intervention, attending a recruitment meeting, and thereby being provided with the opportunity to discuss the implications of the trial, head teachers will provide written consent for their school to participate in the trial (which includes adhering to the randomisation outcome, delivering the programme in full, participating in the training and making good use of additional support). They will also consent to allow the research team to collect and use for the purposes of analysis the following: child and teacher online questionnaires (BVQ and SDQ); child-level data held on the school administrative system (ethnicity, free school meal status, SEN status, attendance); programme implementation monitoring data (online teacher lesson records completed by teachers after each KiVa lesson); school observation data; interview data; and implementation costs data.Parents: It is not necessary to obtain parental consent for the intervention as the programme falls within usual curriculum and other institutional activities. However, parents of pupils in the relevant year groups in participating schools will be provided with an opt-out (passive) consent form that they must return to the respective school if they wish their child’s data (from the BVQ/SDQ) to be withdrawn from the research (they cannot withhold consent for the KiVa pupil online survey to be completed as it is part of the programme). If parents do not opt out it is assumed that they consent to the data collected on their child being used in the evaluation. (Neither children nor parents on their behalf may opt out of participating in the KiVa programme as this is being delivered as part of the PSE curriculum, which is a curriculum requirement.) Parents participating in discussions organised as part of the school observations will be required to provide active consent. As the school observations also involve a researcher asking questions of a class of children, headteachers will be encouraged to let parents know that a researcher will be visiting the school and for what purpose. It is not deemed proportional to obtain passive or active parental consent for this because the questions are non-sensitive, no information is collected about individuals per se, and the data are anonymised at source.Children: Consent to take part in the programme is not required as it falls within usual curriculum and other institutional activities. However, pupils in relevant year groups will be required to provide active consent to complete the KiVa pupil online questionnaire, and will be able to stop completing the questionnaire at any time.Focus groups: Headteachers, teachers, parents, children and other stakeholders will be required to provide active written consent to participating in the respective focus groups and to the information they supply being used in the research.

Bilingual (English/Welsh) consent forms will be provided in all cases.

### Project timetables and milestones

Delivery of the intervention is dictated by the school academic year (early September to mid July), so the recruitment of schools, baseline assessments and the training for intervention arm schools need to take place before the academic year 2013–14. The timetable and milestones will be set according to these criteria. Schools will be recruited in March-April 2013 and randomly allocated to intervention and control arms in May 2013. Baseline data will be collected from all schools in June/July 2013 (BVQ and SDQ). Teachers and other staff in intervention arm schools will be trained in June/July 2013. Intervention delivery will commence in intervention arm schools in September 2013. Coaching for staff in these schools will be provided in each of the three terms of the 2013–2014 academic year. Follow-up outcome data (12 months post-baseline) will be collected in all schools in June/July 2014. This follow-up will overlap with training of staff in control arm schools. Waitlist control arm schools will commence delivery of the programme in September 2014 (after the trial) and receive coaching in each of the three terms of the 2014–2015 academic year. The economic evaluation focuses on intervention arm schools only. Focus groups will take place between February and June 2014, while school observations (including interviews with school personnel) will take place in May/June 2014 for the intervention schools and May/June 2015 for the waitlist control schools. The data analysis will take place at the end of 2015.

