KiVa provides a standard protocol for teachers to address confirmed cases of bullying (the indicated element). Members of the KiVa team meet with the bullied victim and perpetrator(s) separately. If there is more than one perpetrator, the KiVa team will hold an additional meeting with each of the perpetrators. The discussion with the perpetrator can be approached in either a ‘confrontational’ or ‘non-confrontational’ manner. In the confrontational approach, the teacher refers to the perpetrator’s role in the bullying incident explicitly, before asking them to agree to a plan to address the problem. In the non-confrontational approach, the teacher simply explains that the victim is having a difficult time and asks the perpetrator to commit to ways to help them feel better. High-status peers are encouraged to befriend and support the victim and to work with the teacher to think of ways to do this. A follow-up discussion with both the victim and the bully (or bullies) is scheduled for two weeks later to establish whether the bullying behaviours have stopped, and, if necessary, to repeat the process or ultimately to move to other sanctions.

Support and feedback sessions and a helpline will be provided to assist with any queries and improve school adherence to the intervention protocol. Intervention delivery begins at the start of the school year (September).

Intervention training will be provided in the summer term prior to the academic year in which implementation starts (i.e., June/July 2013 for intervention schools). Accredited KiVa trainers (members of the Finnish KiVa team, JH and SC) will provide training in Bangor and Cardiff respectively. Two members of the teaching/management team from each of the schools will be required to attend the two-day training. Follow-up twilight school-based training sessions will be delivered to all school staff (JH and SC). All Key Stage 2 regular class teachers will then deliver the KiVa curriculum to pupils.

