### Control

Control schools will provide services as usual. PSE is an essential element of the basic curriculum for all pupils at maintained schools in Wales [42]. The PSE curriculum aims to develop and explore pupils’ values and attitudes, equip them to live safe and healthy lives, promote self-respect, celebrate diversity, and empower participation in school and community life as responsible citizens. The PSE Framework states that “it is the responsibility of the school to plan and deliver a broad, balanced programme of PSE to meet the specific need of the learners” (p.3). Control schools will continue to use their existing plan for covering the PSE curriculum. Schools use various strategies to improve social interactions, such as peer support/mentoring schemes (62 % of UK schools [43]), and to prevent or address bullying. No other programmes or strategies will be prohibited during the trial, so that there is no interfererence with standard school practice. The trial uses a waitlist control design and KiVa will be implemented in the control schools after the end of the trial.

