School-wide programme implementation will be assessed by independent observation (one per school, conducted in Spring 2014 for intervention schools and Spring 2015 for control schools). These school observations will be undertaken to look at how the schools are delivering the programme and examine differences and similarities in delivery across different school contexts. School-wide observations will use a list of eight items and researchers will score each one on a three-point scale (0 = “not true”, 1 = “somewhat true”, 2 = “certainly true”) with additional space for recording notes to support the score given. Items cover: the visibility of KiVa materials in the school; the extent to which the headteacher, playtime supervisors, a Key Stage 2 teacher (or the KiVa team lead) and Key Stage 2 pupils can talk fluently and knowledgably about the programme; evidence of a KiVa team logbook being used to record incidents of bullying and how they were dealt with; and whether parents know what the programme is, have received information about it from the school and have used the website (schools will select parents, and it is acknowledged that they will be unrepresentative). Scores on the school observation measure will be summed to give an overall score for each school in the range 0 to 16, where a higher score indicates stronger school-wide implementation. These scores and the observers’ comments will be used to help identify common strengths and weaknesses as regards implementation. Again, analyses will use data on KiVa delivery in intervention and waitlist control schools.

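### Control-school staff are to be trained in KiVa during the follow-up window, and nothing requires the teacher SDQ to be completed first

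*Protocol article*

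**What the plan says.** The timetable is explicit. Under Project timetables and milestones: "Follow-up outcome data (12 months post-baseline) will be collected in all schools in June/July 2014", and directly afterwards: "This follow-up will overlap with training of staff in control arm schools".

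The Intervention section describes the training in two steps. First, "Two members of the teaching/management team from each of the schools will be required to attend the two-day training". Then, "Follow-up twilight school-based training sessions will be delivered to all school staff". Training belongs to the summer term before a school starts delivery. For control schools, which start in September 2014, that is the summer term of 2014.

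The Control section describes the comparator as services as usual and states that "KiVa will be implemented in the control schools after the end of the trial".

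On the observation visits, the timetable says "school observations (including interviews with school personnel) will take place in May/June 2014 for the intervention schools", while Implementation fidelity says they are "conducted in Spring 2014 for intervention schools and Spring 2015 for control schools".

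**The concern.** Six secondary outcomes are teacher-completed SDQ scores: emotional difficulties, conduct, peer relations, prosocial behaviour, total difficulties and impact (Outcome measures). The people who supply these scores in control schools are among the staff due to be trained in the same weeks.

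The article itself gives a reason to expect that training could alter what teachers report. Its Background notes that teachers pick up fewer bullying incidents than pupils do and judge them milder, and concludes that teachers need awareness training. A control teacher who has just been trained may therefore notice or score more difficulties, which would favour KiVa. The teacher may equally start to respond differently to pupils, which would dilute the contrast. The six-month recall of the SDQ does not fully protect against the first, because a trained rater scores the whole period with the new frame of reference.

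There is a smaller, related point. In 2014 only intervention schools receive observation visits, at which a researcher questions a class about KiVa. Those visits can fall in the same weeks as the pupil survey.

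**Working it through.** The plan gives no figure for this point, so the check sets its statements side by side and then bounds how many raters could be affected.

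**Order of events in control schools**

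| Event | Timing | Section |
|---|---|---|
| Pupil survey and teacher SDQ | June/July 2014 | Data collection; Project timetables and milestones |
| KiVa staff training | Overlaps with the above | Project timetables and milestones |
| End of school year | Mid July | Project timetables and milestones |
| Start of KiVa delivery | September 2014 | Project timetables and milestones |

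No section fixes the order of the first two rows within a school. The whole-staff sessions follow the central course but are undated.

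**Outcomes exposed**

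- SDQ, six scores: rated by teachers, so exposed directly if the rater is trained first.
- Victimisation (primary) and perpetration: reported by pupils about recent months (Victimisation and bullying). Exposure is indirect, through newly trained staff, and confined to the end of the recall period.
- Absence: taken from school records for the academic year (School absenteeism), so essentially unexposed.

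**How many raters could be trained first**

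Inputs from Sample size: 1.25 classes per year group, four year groups, 10 control schools. Assumption not in the article: one SDQ rater per class, with similar numbers of pupils each.

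- Raters: 1.25 × 4 × 10 = 50.
- Central course: 2 × 10 = 20 staff.
- If every school rates before training: 0 of 50.
- If only the central course comes first and both attendees are raters: at most 20/50 = 40%. It is less if managers attend.
- If the whole-staff sessions also come first: up to 50 of 50.

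**Size of any shift**

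If a fraction f of control ratings is made after training and each moves by δ SD, the arm mean moves by f × δ. The article gives no δ. For an assumed δ of 0.05 to 0.2 SD:

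- f = 0 gives 0
- f = 0.4 gives 0.02 to 0.08 SD
- f = 1 gives 0.05 to 0.20 SD

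The sign is unknown. These figures show only how the result depends on f and δ; they are not an estimate.

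**Observation visits**

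May/June (visits) and June/July (survey) share June. Spring and May/June are compatible as loose wording, since May falls in spring. The fault is the possible overlap with the survey, not a contradiction between the two sections.

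**Parallel at baseline**

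Intervention staff are trained in June/July 2013, after allocation in May 2013 and in the same window as the baseline SDQ. The order within a school is not fixed there either.

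**The case against.** The strongest reply is that the overlap concerns staff training, not delivery. Control pupils receive no lessons before follow-up, and KiVa starts in those schools in September 2014. A reader might infer from the timetable that the usual-provision comparator is contaminated; the article does not support that. The reply stands.

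Second, the overlap is stated for the arm as a whole. An individual school could still complete its SDQ first, and the number of raters trained beforehand is unknown. This also stands, and it is why no size can be given. It does not remove the point: the article plans the overlap openly and sets no order within it, so this is more than operational detail left to a fuller document.

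Third, rating conditions differ between arms under any schedule. Intervention teachers are trained, have delivered KiVa for a year and know their allocation. Training some control raters might even bring the two arms' frames of reference closer. This stands as a limit on what rescheduling can achieve. A mixture of trained and untrained control raters, depending on local dates, is still an avoidable complication.

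Fourth, a reader might infer that the observation visits prime intervention pupils just before they report the primary outcome. The article does not show this. The order of visit and survey is not given, there is one visit per school, the questions go to one class and are described as non-sensitive (Informed consent), and by then pupils have had most of a year of lessons.

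**Conclusion.** The point holds as a risk of rater bias in the six teacher-rated SDQ scores, of unknown size and direction. It rests on two facts in the article, the planned overlap and the training of all school staff, and on the absence of any rule that outcomes come first.

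It does not extend to a claim that the primary result is compromised. Victimisation is self-reported by pupils, and only an indirect effect through newly trained staff is conceivable. Nor is it sound to set an assumed shift of 0.1 SD against the Finnish perpetration effect (d = 0.10) and call them equal. The shift is chosen rather than derived, the two outcomes differ in kind and in reporter, and the comparison needs every control rater to be trained before rating.

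The observation visits are a minor scheduling matter. The plan should be changed because the remedy is cheap, not because the damage has been shown to be large.

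**What to change.** 1. State that in each control school the teacher SDQ and the pupil survey are completed and locked before any member of its staff attends KiVa training, whether the central course or a twilight session.
2. Record the completion dates and the training dates by school.
3. Where the order cannot be kept, run a sensitivity analysis that excludes SDQ ratings made after training.
4. Schedule the intervention-school observation visits outside the follow-up survey window, and give the same dates under Implementation fidelity and Project timetables and milestones.

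The cost is mainly scheduling, but it is real. Term ends in mid July and control delivery starts in September 2014, so the central course and the whole-staff sessions must fit into a shorter period after the survey. The change does not remove the remaining asymmetry that intervention-arm teachers are trained and aware of allocation. That should be acknowledged when the SDQ results are interpreted.

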#### Social and emotional well-being

In order to measure aspects of children’s social and emotional well-being (also secondary outcomes), the teacher-reported Strengths and Difficulties Questionnaire (SDQ) [44, 45] will be administered at baseline and at 12-month follow-up. It is a 25-item screening measure widely used in developmental, social, clinical and educational studies to measure children’s mental health and well-being. The teacher version can be completed for children aged 4 to 17 years. It comprises five subscales (each with 5 items) assessing hyperactivity, conduct, emotional difficulties, peer relations and pro-social behaviour, respectively, over the past six months. There are three response options for each item (0 = “not true”, 1 = “somewhat true”, 2 = “certainly true”). For each of the subscales the score can range from 0 to 10; a higher score indicates more problems for all subscales apart from the prosocial subscale, for which a higher score indicates more prosocial behaviour. The “total difficulties score” is calculated by summing the 20 items that comprise the first four subscales listed above (total score ranges from a possible 0 to 40, with higher scores indicating greater problems).

The SDQ also has a brief ‘Impact supplement’ which starts with a single question about whether the child has difficulties with emotions, concentration, behaviour, or being able to get on with other people (response set: “No”, “Yes – minor difficulties”, “Yes – definite difficulties”, and “Yes – severe difficulties”). If the answer is “Yes” there are four additional questions, focusing respectively (in the teacher version) on: chronicity, or duration (response set: “less than a month”, “1–5 months”, “6–12 months”, “over a year”); distress to the child (response set: “not at all”, “only a little”, “quite a lot”, “a great deal”); impact on the child’s everyday life in terms of peer relations and classroom learning respectively (response set: 0 = “not at all”, 0 = “only a little”, 1 = “quite a lot”, 2 = “a great deal”); and burden to the teacher or class as a whole (response set: 0 = “not at all”, 0 = “only a little”, 1 = “quite a lot”, 2 = “a great deal”). The teacher-report impact score is calculated by summing responses to three items, namely (i) whether the difficulties upset or distress the child, and impact on (ii) peer relations and (iii) classroom learning, with the total score ranging from 0 to 6, where higher scores indicate greater impact.

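### KiVa training of control-school staff is planned to overlap the only follow-up measurement, and no rule has each school's data, above all the teacher SDQ, collected first

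*Protocol article*

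**What the plan says.** All places are in the protocol article.

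- **Project timetables and milestones:** "Follow-up outcome data (12 months post-baseline) will be collected in all schools in June/July 2014". Two sentences of the same paragraph are then enough to set the problem, the second being: "This follow-up will overlap with training of staff in control arm schools". Programme delivery in control schools starts in September 2014.
- **Control:** "Control schools will provide services as usual", and "KiVa will be implemented in the control schools after the end of the trial".
- **Table 1:** the control arm is shown as receiving usual provision from September 2013 to July 2014. The follow-up window lies inside that span.
- **Intervention:** two staff per school attend a two-day course, and then "Follow-up twilight school-based training sessions will be delivered to all school staff". The dates given there are for the intervention schools in 2013. No different package is described for control schools.
- **Social and emotional well-being:** "the teacher-reported Strengths and Difficulties Questionnaire (SDQ) [44, 45] will be administered at baseline and at 12-month follow-up".
- **Outcome measures:** the teacher SDQ supplies six outcomes: emotional difficulties, conduct problems, peer relations, prosocial behaviour, total difficulties and impact.

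No section says that a control school finishes its pupil survey and SDQ before its staff are trained.

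**The concern.** A waitlist control arm is meant to show what happens without the programme. Here one part of the programme, staff training, may reach control schools while their follow-up data are still being collected. Whether a teacher rates pupils before or after that training would depend on how dates happen to be booked.

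The SDQ is where this matters most. Its raters are teachers in the schools being trained, they know their school's allocation, and the training deals with recognising bullying and responding to it. Training could change how a teacher judges peer problems or distress on the day the form is completed. No later wave exists to fall back on, and no analysis can restore the order once the data are in.

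The pupil survey carries a weaker version of the same worry, through how staff respond to bullying or how they explain it when pupils answer.

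**Working it through.** The article gives no figure on this point to reproduce, and the sample size is not in question. The check is on timing, on who is exposed, and on whether a bias could be signed.

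**1. Is the overlap real?** Yes. It is stated outright, and it concerns the one post-baseline wave. It also falls inside the period that Table 1 labels as usual provision.

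**2. Who could be exposed?** If control schools receive the package set out under Intervention, the twilight sessions reach all staff, including the teachers who rate the SDQ. Control pupils receive no lessons until September 2014. The number of the 10 control schools that would be trained first is not stated and could be none.

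**3. How much of the recall period could follow training?** Inputs: follow-up in June/July, a school year ending in mid July, a primary item asking about roughly the last two months, and an SDQ asking about six months. Assumptions: the earliest training is on 1 June, the latest survey is on 15 July, two months are 61 days and six months are 183 days. The largest possible gap is then 44 days.

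Share of recall after training = gap / recall length.

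| Gap | Primary item | SDQ |
|---|---|---|
| 7 days | 7/61 = 11% | 7/183 = 4% |
| 14 days | 14/61 = 23% | 14/183 = 8% |
| 44 days (extreme) | 44/61 = 72% | 44/183 = 24% |

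For the primary item, most of the recall period precedes training unless the gap passes 30 days. For the SDQ, recall is not the main route. The rating is a judgement made on the day, so even a short gap could matter.

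**4. Can the SDQ bias be signed?** Suppose training shifts a teacher's rating by *s*, of unknown sign and equal in both arms. Let *q* be the share of control ratings made after training in 2014. Let *b* be the share of intervention ratings at baseline made after training in 2013, since that training shares the June/July 2013 window with baseline collection. Let *β* be the baseline slope in the adjusted analysis.

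- Intervention raters at follow-up are all trained, so they carry *s*. Control raters carry *q·s* on average.
- The raw offset in the arm difference is *s*(1 − *q*).
- After baseline adjustment the offset is *s*(1 − *q* − *βb*).

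The documents give none of *s*, *q*, *b* or *β*, so neither the sign nor the size follows.

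**The case against.** The strongest case on the other side has four parts.

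- **A shared window is not a breach.** The article shows two activities in the same weeks. It does not show any control school being trained before it is surveyed. This stands, and the point is one of risk.
- **Training is not delivery.** A reader might infer that the overlap contradicts the Control section. It does not: that section speaks of implementing KiVa after the trial, and the timetable agrees by starting delivery in September 2014. What sits awkwardly is only the usual-provision label in Table 1.
- **Training control raters might narrow a gap.** Intervention teachers have been trained, have worked with KiVa for a year and know their allocation. If training changes rating thresholds, training control teachers could bring the arms closer together. This also stands, and it is why no direction is claimed. The case for fixing the order is that it gives the control arm one defined condition at measurement.
- **A condensed article leaves school-level scheduling to the full protocol.** That is true of dates for single schools. The overlap itself is a stated choice and not an omitted detail.

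A reader might also turn the overlap into a loss of power by assuming that the control victimisation rate falls by a point or two. Nothing in the article supports such a fall from staff training in the last weeks of term, and a rise through more reporting is just as open.

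**Conclusion.** The point holds as a precaution, mainly for secondary outcomes. The plan accepts that KiVa training of control staff will overlap the only follow-up wave and states no order within a school. Six SDQ outcomes are exposed, in anything from none to all of the 10 control schools.

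No numerical bias can be given. That conclusion rests on training not being dated by school, and on intervention raters being trained and unblinded as well. The exposure of SDQ raters assumes that control schools receive the training package described under Intervention.

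The risk to the primary outcome is smaller. Pupils report it, they have no KiVa lessons before September 2014, and most of their recall period precedes training unless more than a month separates the two. To say that the primary comparison is contaminated would go beyond the text.

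**What to change.** Amend Project timetables and milestones and Table 1 as follows.

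1. Each control school closes its teacher SDQ and its pupil survey before any of its staff attend KiVa training or a twilight session.
2. The same survey weeks apply in both arms.
3. Survey and training dates are logged for each school.
4. If any control school was trained first, the full intention-to-treat analysis stays primary, and a sensitivity analysis without the affected data is reported beside it.

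The cost is less freedom in booking. It is greatest if control-arm training is central and shared, as it was in Bangor and Cardiff for the intervention schools, because every school attending must then finish its data collection before one date, in a window that ends in mid July. Leaving out affected schools also costs precision in an arm of 10, which is why that analysis should stay secondary. The sample size need not change. The fix does not remove the general weakness of unblinded teacher ratings; it only ensures that the control arm is measured before KiVa training reaches it.
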